#### Participants

We aimed to recruit at least 500 eligible participants (see below for inclusion and exclusion criteria) with normal cognition from the ISLAND Project. As of March 2024, we have recruited 1382 adults, with mean (SD) age 66.20 (7.65) years, range 50–92 years, and 72.07% female. The ISLAND project was launched in October 2019 at the University of Tasmania as a 10-year prospective cohort study of Tasmanians ≥ 50 years old with nested interventions to reduce dementia risk [45, 46]. To date, > 14,000 people have been recruited to the ISLAND Project; 8,500 research participants (mean age 63 years) have provided detailed demographic and health data, 3,000 have completed the online validated Cambridge Neuropsychological Test Automated Battery (CANTAB) cognitive tests [47], 1,800 have completed online motor-cognitive tests (TAS Test) [38] and more than 1,500 have provided blood samples. Paired Associates Learning (PAL) scores distinguish between older adults with MCI and those who are cognitively healthy with a sensitivity/specificity of 0.83/0.82 [48]. The online ISLAND Project surveys are repeated annually with cognitive performance and blood-based biomarkers collected every second year.

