#### Design

There will be three sub-studies to address Aim 2 as follows: Study 2.1, a cross-sectional study of 30–40 adults to determine validity of data collection from different types of smartphones; Study 2.2, a prospective cohort study of 50–100 adults ≥ 50 years old to assess usability and reliability, and Study 2.3, a prospective cohort study of ∼1,000 adults ≥ 50 years old to assess validity against cognitive measures. The methods to addresses Aim 2 are summarised in Fig. 4. The TapTalk test protocol on a smartphone will be based upon the findings in Study 1 and comprise around three to five of the most discriminating hand and speech-like movements, aiming for test duration of approximately 2–3 min. The TapTalk protocol may be further refined after studies 2.1 and 2.2, depending on user feedback and results.

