##### Study 2.3

We will undertake an 18-month prospective study of approximately 1,000 ISLAND Project participants who have completed online cognitive CANTAB tests in 2021. Participants in the ISLAND Project [45, 46] are invited to complete online CANTAB cognitive tests every 2 years. The first testing period was mid-2021 and ∼3,000 participants completed the tests; these participants will be invited to take part in the TapTalk prospective validity study. Every 6 months over an 18-month period (four data collection points in total; T0, T + 6, T + 12, T + 18), eligible participants will be invited via the ISLAND Project website (‘portal’), to complete TapTalk at any time over the next one-month period. Participants will be asked to complete TapTalk on their own smartphone at home or in a setting of their choice. Consent will be taken at each data collection point. When participants complete the TapTalk app they will be asked to complete a questionnaire about user experience and symptoms relating to hand and speech function (see supplementary files). The whole procedure, including the questions and tests, is expected to take about 5 min. A reminder email will be sent 1, 2 and 3 weeks after the initial invitation to people who have not yet completed the test.

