#### Statistical analysis

The data from participants who complete TapTalk on two or more occasions over an 18-month period, and CANTAB on two occasions (2021 and 2023) will be included in the analysis. De-identified ISLAND Project participants will be classified as cognitively ‘stable’ or ‘declining’ using longitudinal CANTAB cognitive scores. TapTalk scores will be calculated using algorithms developed in Study 1. Logistic regression will be used to estimate the odds of a participant being confirmed as ‘declining’ at time T_2_ (24 months) conditioned on TapTalk score at time T_1_ (12 months). The overall outcome of Study 2 will be a smartphone app, TapTalk, that is usable, reliable and validated against established online CANTAB cognitive tests.

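### Study 2.3: the CANTAB years and the 12- and 24-month model times fit no single clock, so the TapTalk predictor would probably follow the decline it is meant to predict

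*Protocol article*

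**What the plan says.** All references are to the protocol article, Methods.

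- **Outcome data.** Under Study 2.3, CANTAB participants "are invited to complete online CANTAB cognitive tests every 2 years", and "The first testing period was mid-2021". The Study 2.3 statistical analysis admits people with at least two TapTalk completions in 18 months "and CANTAB on two occasions (2021 and 2023) will be included in the analysis". They are classed as stable or declining "using longitudinal CANTAB cognitive scores". The Aim 2 sample size justification describes the same complete cases as having CANTAB at baseline and at 24 months.
- **Model.** A logistic regression estimates the odds of being confirmed as declining "at time T_2_ (24 months) conditioned on TapTalk score at time T_1_ (12 months").
- **TapTalk schedule.** There are "four data collection points in total": T0 and 6, 12 and 18 months later. No calendar date is given for T0.
- **Order of development.** The Aim 2 design section states: "The TapTalk test protocol on a smartphone will be based upon the findings in Study 1". The Study 2.3 analysis scores TapTalk with the Study 1 algorithms. The Study 2.2 analysis section places the Study 2.3 invitation after refinements based on Study 2.2.
- **State of Study 1.** The Aim 1 participants section says: "As of March 2024, we have recruited 1382 adults". The Setting section speaks of the software adaptation in the future tense, and the Aim 1 sample size section says the biomarker combination defining a positive case is still to be decided.

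**The concern.** A prediction model needs its predictor measured before its outcome. Here the analysis set is tied to CANTAB waves in 2021 and 2023, while the predictor comes from an app whose tasks and scoring wait on a study that was unfinished around March 2024. If the 2021 and 2023 waves define decline, the TapTalk score used in the model would be recorded after the decline had been observed.

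The regression would still run and return an odds ratio, but it would answer a different question: whether people who have already declined tap and speak differently afterwards. That is of some interest as validity evidence. It cannot support the statement in the Abstract's discussion that the study will estimate risk of cognitive decline, nor the description of Study 2.3 as prospective.

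The inclusion rule adds a separate mismatch. It asks for any two TapTalk completions, whereas the model uses one particular score, the one at 12 months.

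**Working it through.** **1. The plan's own interval.** Taking mid-2021 as July 2021, July 2021 + 24 months = July 2023. This reproduces both the pair of years and the description as baseline and 24 months, so the natural reading is that the 24-month outcome is the 2023 wave.

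**2. Clock started at CANTAB 2021.** T1 = July 2021 + 12 = July 2022, and T2 = July 2023. A smartphone TapTalk score would be needed in mid-2022. That does not fit an app built from Study 1 findings when Study 1 was still described largely in the future tense around March 2024.

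**3. Clock started at TapTalk T0.** T0 is not stated, so it is varied. The month of the 2023 CANTAB is not stated either; July and December are used. A month earlier in 2023 would widen every gap.

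| Assumed T0 | T0 + 12 | T0 + 24 | T0 + 12 minus July 2023 | T0 + 12 minus December 2023 |
|---|---|---|---|---|
| October 2023 (registration) | October 2024 | October 2025 | 15 months | 10 months |
| March 2024 (recruitment count) | March 2025 | March 2026 | 20 months | 15 months |
| September 2024 (illustration) | September 2025 | September 2026 | 26 months | 21 months |

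In every row the 12-month score falls after the 2023 CANTAB, and the 24-month point cannot be the 2023 wave.

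**4. How early T0 would have to be.** For the 12-month score merely to coincide with or precede the 2023 CANTAB, T0 must be no later than July 2023 − 12 = July 2022, or December 2023 − 12 = December 2022. For the stated 12-month lead, T0 must be no later than July 2023 − 24 = July 2021, or December 2021.

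**5. Inclusion rule against predictor.** With four collection points, the completion patterns with at least two completions number 6 + 4 + 1 = 11. Those lacking the 12-month score are the 3 pairs and 1 triple formed from T0, 6 and 18 months, so 4 of the 11 qualifying patterns cannot supply the predictor. Someone with only the 12-month score is excluded although the model needs no other TapTalk score. These are counts of patterns, not of people.

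**6. Consequence for the sample size statement.** More than 1,000 complete cases out of 3,000 is about 1,000 / 3,000 = 33%. That figure uses the two-completion rule, so it does not count the people who can enter the model. The article gives no retention inputs from which to derive a replacement.

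**The case against.** The strongest reply is that the timing is inferred. No T0 is given. The March 2024 figure is a recruitment count, not a closing date, and the target of at least 500 may have been met earlier. Registration was retrospective, which suggests earlier activity. The years 2021 and 2023 appear in the sentence on whose data are analysed, while the sentence on classification names no years, and later CANTAB waves follow from the two-yearly schedule.

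Much of this stands, and it limits what can be claimed. A reader might infer that no analysed participant could have any TapTalk score before the outcome CANTAB. The documents do not establish that: with T0 in October 2023 and a December 2023 CANTAB, the T0 score would come two months earlier. The score the model uses is the 12-month one, however, and reversing its order would need T0 in 2022 or before, which the development sequence makes implausible. If later waves are meant for the outcome, the named years and the baseline-and-24-months description are wrong and still need correcting.

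A reader might also infer that the Study 2 validity claim collapses. It does not. The claim is validation against CANTAB tests in general, and an association with recent decline is some evidence of that. The Study 1 algorithm and Aim 3 do not depend on this outcome.

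Two further inferences fail. Conditioning on a score is ordinary regression language and asserts no time order. The absence of a 24-month TapTalk point is no defect, because 24 months is the outcome time. The inclusion mismatch is secondary and might be settled in an analysis plan that is not shown, but the article does state a rule, and it does not match the stated model.

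**Conclusion.** The point holds as a contradiction in stated rules, not as a missing detail. The CANTAB years, the 12- and 24-month model times and the development sequence cannot all be true on one clock. Followed as written, the 12-month TapTalk score would come about 10 to 20 months after the 2023 CANTAB, and later still if T0 is after March 2024. The odds ratio would then be one of association with earlier decline, reported as prospective prediction.

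The size rests on two assumptions: T0 between October 2023 and March 2024 or later, and a 2023 CANTAB between July and December. The direction is much less sensitive, since it changes only if T0 fell in 2022 or earlier. The inclusion mismatch does not depend on any calendar date.

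**What to change.** Define the CANTAB waves relative to each participant's TapTalk: a baseline wave at or before T0, and an outcome wave after the TapTalk score used as predictor. Both can come from the existing two-yearly schedule, for example 2023 and a later wave. State which clock T1 and T2 refer to.

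Report the interval from TapTalk to outcome, or adjust for it, because it will vary. If later waves fall in July, T0 in March 2024 puts the 12-month score in March 2025, 4 months before a July 2025 wave and 28 months before a July 2027 wave. T0 in September 2024 misses July 2025 and leaves 22 months to July 2027. The documents give no ground for preferring the T0 score to the 12-month score. Whichever is chosen, simply taking the next wave after it leaves the lead time uncontrolled.

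If the 2021 and 2023 waves are kept, describe the result as association with prior decline and drop the prospective claim for this analysis.

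In either case, replace the two-completion rule with a requirement for the TapTalk score in the model plus both CANTAB waves, and restate the figure of more than 1,000 complete cases on that basis.

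The cost is mainly wording. No new tests are needed. Re-dating brings a later readout and probably some further loss to follow-up; relabelling costs no time but gives up the predictive claim.

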### Statistical analysis

We will use data from 350 of a sample of 500 participants to develop multivariable models that classify data according to risk of preclinical AD pathology. Data from the remaining 150 will determine the externally validated sensitivity/specificity of candidate models in detecting preclinical AD. Hand-speech movement data will be normalised. Participants with blood biomarker levels in the preclinical AD range (e.g., p-tau 181, or a combination of blood biomarkers) will be classified as ‘AD positive’. We will use penalised logistic regression to measure the associations between movement patterns and AD positivity. Covariates may include age, gender, apolipoprotein E ([APOE] a risk gene for AD analysed through blood sampling as part of the ISLAND Project), years of education, and handedness. As a secondary, more agnostic approach, we will use deep learning methods to discover features in movement and speech-like data that map to AD positivity.

We will use cross-validation to avoid overfitting by selecting penalty terms (type and amount of shrinkage applied to coefficients) which optimise the bias-variance trade-off. Bootstrap procedures will be used to estimate model uncertainty. We will externally validate models using data from the remaining 150 participants. Receiver Operating Characteristic (ROC) curves will be plotted against the positive AD cut-off to assess the sensitivity/specificity of movement and speech-like models to discriminate the preclinical AD stage from normal ageing. The model with the highest area under the ROC curve (AUC) will be chosen as the TapTalk algorithm.

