### Sample size justification

The precise combination of blood-based biomarkers used to determine ‘positive’ preclinical AD pathology is yet to be determined as the scientific literature is developing quickly and new biomarkers are being developed regularly. We will review the literature before deciding on the best biomarker test, or combination of tests, that should be used to define AD pathology risk most accurately.

Currently p-tau 181 is considered one of the most accurate blood-based biomarkers for preclinical AD risk and we have therefore based our sample size calculation on this biomarker. As new tests are developed and are likely to be even more sensitive/specific than p-tau 181, the current calculation is a conservative estimate. We estimate that 17% of cognitively normal adults within our cohort have p-tau 181 in the preclinical AD range [55]. There are no tests of DDK compared to AD biomarkers, so we have based all calculations on finger tapping data.

We have performed ROC curve analysis using open data from Mollica et al. to calculate sensitivity and specificity of finger tapping speed and variability to predict CSF p-tau 181 [20]. This showed area under ROC curve (AUC) of 0.75 for a null linear model including age, gender and years of education, but not finger tapping. We calculated that the sample size to compare a screening test with an AUC > 0.90 against the null model requires 60 preclinical AD cases (positive p-tau181) and 290 healthy ageing controls (negative p-tau181). Thus, we will use 350 in the development dataset (expected 60 [17%] preclinical AD cases) and 150 in the validation dataset (expected 25 [17%] preclinical AD cases) to test cut-offs from the development model. The PROBAST tool [56] for assessment of prediction and diagnostic method studies confirms these development and validation strategies have a low risk of bias.

### AIM 2

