### Sample size justification

Using CANTAB cognitive test responses already collected in the ISLAND Project (n = 3,000), we estimate that we will collect > 1,000 complete cases (TapTalk app completion twice in 18 months and CANTAB at baseline and 24 months), which is ample for logistic regression with a single fixed-effect predictor variable.

### AIM 3

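### Study 2.3 states only a measure of association, with no discrimination measure or criterion, yet words its outcome as an app validated against CANTAB

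*Protocol article*

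**What the plan says.** Under Aim 2, Study 2.3, Statistical analysis, participants are classed as stable or declining "using longitudinal CANTAB cognitive scores". The stated analysis is then: "Logistic regression will be used to estimate the odds of a participant being confirmed as" declining at 24 months, conditional on the TapTalk score at 12 months. The same paragraph closes by giving the overall outcome of Study 2 as an app that is "usable, reliable and validated against established online CANTAB cognitive tests".

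The sample size justification for Aim 2 reads "we estimate that we will collect > 1,000 complete cases", "which is ample for logistic regression with a single fixed-effect predictor variable". It gives no effect size, alpha, power, expected proportion declining or precision target.

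Elsewhere the article uses accuracy measures. In Aim 1, Statistical analysis, ROC curves give sensitivity and specificity, and "The model with the highest area under the ROC curve (AUC) will be chosen as the TapTalk algorithm". The Aim 1 sample size is built around "a screening test with an AUC > 0.90 against the null model". In Aim 3, Statistical analysis, AUCs with bootstrap 95% confidence intervals are planned, with Youden cut-offs and a comparison of sensitivity and specificity.

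**The concern.** An odds ratio describes how the odds of decline change with the score across the whole group. It does not say how far the score distributions of decliners and stable participants overlap, and that overlap decides whether a score can sort individuals. In a large sample, a small shift between two heavily overlapping distributions still gives a clear association.

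Study 2.3 is the part of the project that follows the smartphone score forward to later cognitive decline. The Abstract and Discussion speak of screening individuals and stratifying risk, and those claims need discrimination. As written, nothing links the estimated odds to the word validated. A reader of the results could not tell from the stated analysis whether the app separates decliners from stable people well, poorly or hardly at all.

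**Working it through.** **The plan's own figure.** More than 1,000 complete cases out of about 3,000 is a recruitment estimate of at least one third. It is not a power calculation, so there is no formula to reproduce. Its adequacy for fitting can be checked: with one predictor, 5% to 30% declining gives 1,000 × 0.05 = 50 to 1,000 × 0.30 = 300 events for that predictor. The sample is indeed ample for fitting the model, but this says nothing about accuracy.

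**Inputs.** From the article: n = 1,000, one predictor, a binary outcome. Assumed, because the article does not state them: two-sided alpha 0.05, power 80%, proportion declining p = 5% to 30%, and a roughly normal score with equal variance in both groups.

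**Formulas.**
- Detectable log odds ratio per SD: β = (1.96 + 0.8416)/√(n p(1−p))
- Standardised difference between decliners and stable participants: d = β/√(1 − p(1−p)β²)
- AUC = Φ(d/√2)
- Sensitivity = specificity at the Youden cut-off = Φ(d/2)

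Example at p = 10%: n p(1−p) = 90, so β = 2.8016/9.487 = 0.295 and the odds ratio is e^0.295 = 1.34. Then d = 0.296, AUC = Φ(0.210) = 0.58, and sensitivity = specificity = Φ(0.148) = 0.56.

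| Declining | Odds ratio per SD, 80% power | AUC | Sens. = spec. | AUC if only just significant | Power when true AUC is 0.60 |
|---|---|---|---|---|---|
| 5% | 1.50 | 0.61 | 0.58 | 0.58 | 70% |
| 10% | 1.34 | 0.58 | 0.56 | 0.56 | 93% |
| 20% | 1.25 | 0.56 | 0.54 | 0.54 | 99.5% |
| 30% | 1.21 | 0.555 | 0.54 | 0.54 | 99.9% |

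The just-significant column uses 1.96 alone in the numerator of β. As a check on the approximation, 1,000 simulated logistic regressions at each of the four rates gave power of 0.79 to 0.83 and mean AUCs of 0.613, 0.585, 0.564 and 0.555.

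**What the same data could deliver.** Hanley-McNeil half-widths of the 95% CI for the AUC at n = 1,000:

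| Declining | True AUC 0.70 | True AUC 0.80 |
|---|---|---|
| 5% | ±0.083 | ±0.075 |
| 10% | ±0.059 | ±0.053 |
| 20% | ±0.044 | ±0.039 |
| 30% | ±0.037 | ±0.033 |

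The planned sample therefore supports a usable estimate of discrimination.

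**The case against.** The best reply has four parts.

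*No decision rule is stated.* A reader might infer that TapTalk will be declared validated as soon as the odds ratio is significant. The article does not say so. It gives no test, alpha or threshold for Study 2.3, and it does not use the term odds ratio there. The Discussion leaves failure open, since it makes the promised use conditional on validation and lists insufficient accuracy as a risk. This part stands, and the point is limited accordingly: the stated analysis and the stated outcome are not connected by any criterion.

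*AUC is routine output and could be left to an analysis plan.* This stands in part. Nothing excludes an AUC, and its absence alone would be no finding in a condensed article. But the article does name AUC for Aims 1 and 3 at the same level of detail, and for Study 2.3 it names another measure and attaches the validity claim to it.

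*Association with later decline is a recognised form of predictive validity, and the stated goal is to estimate risk.* This is fair. Logistic regression is not a wrong model here and should stay. It does not by itself support use as a screening test for individuals.

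*Under the model above, AUC and odds ratio per SD carry the same information.* This is correct. With a null standard error of √((n+1)/(12 n₁n₂)), where n₁ and n₂ are the group sizes, an AUC differs from 0.5 at about 0.56, 0.545 and 0.54 for 10%, 20% and 30% declining. Testing the AUC against 0.5 would thus gain nothing. The gain comes from showing the AUC on a scale that reveals its size, with its lower limit, and from a minimum set in advance.

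**Conclusion.** The point holds as a mismatch between analysis and conclusion. Study 2.3 states an association measure only, and the outcome is worded as validation. At n = 1,000, the association detectable with 80% power corresponds to an AUC of about 0.61 to 0.55 over 5% to 30% declining. The alpha, power, decline rate and normal-score model behind these figures are assumptions.

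It would go too far to say that accuracy barely above chance would pass at any decline rate: at 5% declining the detectable AUC is about 0.61, which is poor but not negligible. The AUC above 0.90 in Aim 1 is a planning value for biomarker status. It shows the scale on which the article thinks about accuracy, but it is not a threshold for CANTAB decline. The regression itself is valid; the wording of what it would establish needs repair.

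**What to change.** In Study 2.3, Statistical analysis:

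- Name the AUC of the TapTalk score for CANTAB decline, with a 95% CI, as the main validity measure. Keep the odds ratio as supportive.
- Word the Study 2 outcome by the AUC and its lower confidence limit, not as validated outright. Ideally state a minimum AUC beforehand; without one, a near-chance AUC could still be given the same label.
- If sensitivity and specificity are reported, use a cut-off fixed in advance for the smartphone version and say where it comes from. A reader might think of carrying the Study 1 cut-off forward unchanged. The article does not support that: it is set against blood-biomarker positivity on the full computer version, whereas the smartphone test is shortened, may be refined after Studies 2.1 and 2.2, and is here compared with CANTAB decline.

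The cost is a change of wording. The data and sample size stay the same. The downside is a headline that may look less favourable than a clear odds ratio.

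### Study 2.3 relates 0–24-month CANTAB decline to a TapTalk score taken midway through that window, so the odds ratio mixes concurrent association with prediction

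*Protocol article*

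**What the plan says.** The Study 2.3 statistical analysis uses participants with at least two TapTalk completions and "CANTAB on two occasions (2021 and 2023". They are "classified as cognitively ‘stable’ or ‘declining’ using longitudinal CANTAB cognitive scores". The model then estimates the odds of "being confirmed as ‘declining’ at time T_2_ (24 months", "conditioned on TapTalk score at time T_1_ (12 months".

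The Aim 2 sample size section describes a complete case as "TapTalk app completion twice in 18 months and CANTAB at baseline and 24 months", and treats the analysis as "logistic regression with a single fixed-effect predictor variable".

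The Study 2.3 description sets out the TapTalk schedule: "four data collection points in total; T0, T + 6, T + 12, T + 18". It calls the work a prospective validity study. It recruits people who had already taken CANTAB in 2021.

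**The concern.** With only two CANTAB occasions, 'declining' can only mean change over the whole interval between them. A predictor measured in the middle of that interval can be associated with the outcome in two ways: it may register decline that has already happened, or it may forecast decline still to come. The model has one predictor and no intermediate CANTAB, so nothing in it separates the two.

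The wording of the model is that of a forecast, and the article's Discussion expects TapTalk to indicate a person's risk of cognitive decline. Study 2.3 supplies the longitudinal evidence on decline. If its odds ratio is read as predictive, a test that merely reflects present cognitive state could be credited with foresight.

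**Working it through.** **The plan's own figure.** More than 1,000 complete cases are expected from about 3,000 invited, a completion rate of 1,000/3,000 = 33%. No alpha, power, odds ratio or decline rate is given, so the figure cannot be reproduced. Assuming two-sided 5% and 80% power, the smallest detectable odds ratio per SD is exp[(1.96 + 0.84)/√(n·p(1−p))]. At n = 1,000 this is 1.50, 1.34, 1.28 and 1.23 for decline rates p of 5%, 10%, 15% and 25%. The sample size is not the problem.

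**Where the score falls.** The article gives no common origin for T0, T_1_, T_2_ and the CANTAB rounds. Let T0 follow the baseline CANTAB by L ≥ 0 months, since recruits had already taken the 2021 round.
- T_1_ and T_2_ both counted from the CANTAB baseline: 12/24 of the window has passed at the score.
- T_1_ counted from T0, T_2_ from the CANTAB baseline: (12 + L)/24.
- Both counted from T0: (12 + L)/(24 + L).

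Each is at least one half.

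**Effect on the test.** All of the following are assumptions; the article gives none except n.
- n = 1,000; the worst 20% of observed change is called declining; one-sided 2.5% test.
- True baseline cognition has SD 1. Yearly changes are independent with SD s, so the month-12 score carries no information on months 12–24.
- CANTAB error SD is 0.5, so reliability is 1/(1 + 0.25) = 0.8.
- TapTalk correlates r = 0.4 to 0.6 with cognition at the time it is taken.

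True cognition at month 12 shares the first year's change with the observed 0–24-month change D:

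corr = s² / [√(1 + s²) · √(2s² + 2·0.25)]

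The expected test statistic is about r · corr · √n · φ(z₀.₂)/√(0.2·0.8). The last factor is 0.280/0.4 = 0.70, and 0.70 × √1,000 = 22.13. Rejection is Φ(z − 1.96).

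| s | corr | z at r = 0.4 / 0.6 | Rejection |
|---|---|---|---|
| 0.2 | 0.04/(1.020 × 0.762) = 0.0515 | 0.456 / 0.684 | 7% / 10% |
| 0.3 | 0.09/(1.044 × 0.825) = 0.1045 | 0.925 / 1.388 | 15% / 28% |
| 0.5 | 0.25/(1.118 × 1.000) = 0.2236 | 1.980 / 2.969 | 51% / 84% |

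Simulation of the same set-up gives 7–10%, 15–30% and 48–84%. At s = 0.5 the AUC of the month-12 score for 0–24-month decline is about 0.55–0.57. Its AUC for decline in months 12–24 is 0.50.

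**Comparators under the same assumptions.**
- Score unrelated to cognition (r = 0): z = 0, the nominal rate.
- Score taken exactly at the CANTAB baseline: no shared change, the nominal rate.
- Month-12 score against decline after month 12 only: the nominal rate.
- T0 score taken six months after the CANTAB baseline, s = 0.5: the shared variance halves, corr = 0.125/(1.061 × 1.000) = 0.1179, z = 1.043 / 1.565, rejection 18% / 35% (simulation 20–34%).

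**A different model as a cross-check.** Let decline be a state entered with yearly probability h, and let a binary test detect only decline already present. With h = 5–10%, the share of 24-month decliners who had declined by month 12 is h/[h + (1 − h)h] = 51–53%. With h = 0.10 and sensitivity and specificity of 0.7, apparent sensitivity is (0.10 × 0.7 + 0.09 × 0.3)/0.19 = 0.511. The apparent odds ratio is (0.511/0.489)/(0.3/0.7) = 2.4, where the true forward value is 1.

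**The case against.** The strongest reply is that Study 2.3 aims at validity against CANTAB, as its closing sentence says, and that an association between decline and a score tracking current cognition is relevant to that aim. This stands as a reason to report the association. It does not make the association a prediction, and the study is also described as prospective and modelled as a forecast.

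Several stronger readings are tempting, and the article does not support them:
- *A worthless test would look predictive.* It would not: a score unrelated to cognition rejects at the nominal rate. The effect needs a score that tracks present cognition.
- *TapTalk has no forward information.* That is an assumption of the calculation. If half the yearly change variance is a stable personal slope, the month-12 score does predict months 12–24, with AUC 0.53–0.54 at s = 0.3 and 0.54–0.57 at s = 0.5. The planned odds ratio would still not show how much of it is forward.
- *The T0 score precedes the outcome window, so using it is a full cure.* Nothing places T0 at or before the CANTAB baseline; recruitment follows the 2021 round. A T0 score against that earlier baseline leaves some overlap.
- *Unequal earlier exposure to TapTalk biases the month-12 score.* This requires T_1_ to be the T + 12 wave, which the article does not say, and its size cannot be derived.
- *The upper rejection rates are the expected size.* They need a yearly change SD of 0.5, which has no source in the article and may be large for cognitively asymptomatic adults.

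**Conclusion.** The point holds in this limited sense: a stated model places its only predictor at the midpoint of the outcome window, or later, so its odds ratio combines concurrent and predictive association and cannot alone support a claim of predicting later decline. The direction follows from the design whenever TapTalk tracks current cognition. The size does not: rejection without any forward information runs from about 7–10% at a yearly change SD of 0.2 to about 85% at 0.5, against a nominal one-sided 2.5%. Those figures rest on assumed independent yearly changes, CANTAB reliability 0.8, a 20% decline rate and correlations of 0.4–0.6. This concerns what the article fixes, not a detail left to an analysis plan.

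**What to change.** In the Study 2.3 description, its statistical analysis and the Aim 2 sample size section:
- State one time origin for T0, T_1_, T_2_ and the CANTAB rounds.
- For the predictive claim, use the earliest (T0) TapTalk score and count decline only from the CANTAB round nearest to or after that score. If that round precedes the score, say that the remaining overlap is reduced and not removed.
- If the 12-month score against 0–24-month decline is kept, report it as a mixed concurrent and predictive association, not as prediction of decline.

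Cost: the relabelling needs no new data, and the T0 score is already to be collected. A strictly forward analysis may have to wait for a later biennial CANTAB round, and the association will probably be smaller.
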